## Abstract

**Background:**

Clinical practice guidelines advocate engaging stroke survivors in as much activity as possible early after stroke. One approach found to increase activity levels during inpatient rehabilitation incorporated an enriched environment (EE), whereby physical, cognitive, and social activity was enhanced. The effect of an EE in an acute stroke unit (ASU) has yet not been explored.

**Methods/design:**

We will perform a prospective non-randomized before-after intervention study. The primary aim is to determine if an EE can increase physical, social, and cognitive activity levels of people with stroke in an ASU compared to usual care. Secondary aims are to determine if fewer secondary complications and improved functional outcomes occur within an EE. We will recruit 30 people with stroke to the usual care block and subsequently 30 to the EE block. Participants will be recruited within 24–72 h after onset of stroke, and each block is estimated to last for 12 weeks. In the usual care block current management and rehabilitation within an ASU will occur. In the EE block, the ASU environment will be adapted to promote greater physical, social, and cognitive activity. Three months after the EE block, another 30 participants will be recruited to determine sustainability of this intervention. The primary outcome is change in activity levels measured using behavioral mapping over 12 h (7.30 am to 7.30 pm) across two weekdays and one weekend day within the first 10 days of admission. Secondary outcomes include functional outcome measures, adverse and serious adverse events, stroke survivor, and clinical staff experience.

**Discussion:**

There is a need for effective interventions that starts directly in the ASU. The EE is an innovative intervention that could increase activity levels in stroke survivors across all domains and promote early recovery of stroke survivors in the acute setting.

**Trial registration:**

Australian New Zealand Clinical Trial Registry, ANZCTN12614000679684

## Background

Stroke survivors who receive care in an acute stroke unit (ASU) are more likely to be alive and independent compared with general ward care [1]. Characteristics of the ASU considered to contribute to these outcomes include early mobility and multidisciplinary coordinated rehabilitation [2] to prevent immobility-related complications [3] and commence functional recovery early after stroke. Strong evidence indicates that increased engagement in physical activities targeting mobility and arm-hand function early after stroke result in improved functional outcomes [4]. Yet, despite awareness of the positive effects of increased physical activity, available evidence indicates that stroke survivors spend the majority of the day physically inactive and alone early after stroke [5].

Social support has been recognized as an important determinant of health-related quality of life in stroke survivors [6]. The relationship between various types of social support such as emotional, instrumental, or informational support and quality of life is inconsistent [6]. Some studies have found that high levels of social support are associated with larger improvements in functional status [7, 8]. It is argued that social support can offer encouragement, assistance, and increase compliance with treatments [7, 9] and assist in dealing with the consequences of stroke [6]. However, not all aspects of social support may be beneficial; instrumental support may lead to poorer health if someone becomes dependent on the provided assistance [10]. Limited evidence is available regarding cognitive activity after stroke. Cognitive activity such as listening to music during early recovery has been shown to enhance focused attention [11], lessen depressed mood [11], and improve visual attention in those with unilateral neglect [12]. Despite these possible benefits, little is known regarding social and cognitive activity levels in stroke survivors early after stroke.

There is a need to identify interventions that can increase activity levels across physical, social, and cognitive domains and concurrently have a positive effect on outcomes early after stroke. One possible intervention is an enriched environment (EE). In animal research, an EE is defined as an organized stimulating environment to enhance sensory, motor, and cognitive activities [13]. A systematic review and meta-analysis in animal research of stroke has shown that an EE has a positive effect on physical recovery, learning, and exploratory behavior, which includes reduced decline in memory and levels of anxiety [14]. A pilot study of EE in people with stroke was recently undertaken in the sub-acute inpatient rehabilitation setting [15]. This study showed promising results, with increased activity levels demonstrated across these activity domains [15]. An EE was achieved within this study by creating communal areas with stimulating equipment and individual enrichment through provision of personal equipment such as music and hobby activities [15]. An EE can provide activities that are meaningful and tailored to each stroke survivor as a wide variety of activities can be included in an enriched clinical setting. In addition, novel advanced technology such as virtual reality, IPads, and active gaming technologies can be a valuable addition to provide stimulation to stroke survivors with a therapeutic effect [16–18]. Enrichment strategies with a more conventional character could involve music and art, as these activities have shown to reduce boredom and a positive effect on mood in stroke survivors [19, 20].

Taken together, it is plausible that the implementation of an EE immediately post-stroke within an ASU could positively influence activity levels across all domains and lead to fewer complications and improved functional outcomes. This pilot study aims to determine the effect of implementing an EE in an ASU on physical, social, and cognitive activity levels, adverse events, and functional outcomes. We hypothesize that stroke survivors who start their journey in an ASU with an embedded EE will be more active, experience fewer complications, and achieve greater functional outcomes compared to those who start their journey in an ASU without embedded EE.

## Methods/design

The study involves a prospective non-randomized before and after design. We will recruit 30 people with stroke to usual care (block 1) and subsequently 30 to EE intervention (block 2). We will evaluate activity levels across all domains, secondary complications, and functional outcomes within both blocks. Following block 1, we will embed an EE in the same ASU during a 6-week period before commencement of block 2. To determine if embedding an EE within an ASU persists, activity levels will be re-evaluated 3 months post-Block 2 (EE) with an additional 30 stroke participants.

### Participants and setting

All recruitment for this study will be conducted in the same ASU in a regional Australian acute hospital. The ASU is an endorsed unit with 470 stroke admissions per annum, an average acute length of stay of 4.1 days, and an in-hospital mortality rate of 17 %. Rehabilitation by a multidisciplinary team is commenced on the day of admission, with transfer to general inpatient rehabilitation units (public and private) if length of stay is predicted to be greater than 7–10 days. Several community-based rehabilitation services are available spanning home and center based and slower transition care. The ASU has 8 funded stroke beds and is embedded within a 16-bed ward (8 single rooms and 4 double rooms). The ward is supported by 2.0 fulltime equivalent (FTE) physiotherapists, 1.6 FTE occupational therapists, 1.0 FTE speech therapist, 1.0 FTE social worker, 0.5 FTE dietician, and 0.7 FTE therapy assistant.

All stroke survivors admitted to the hospital will be screened for eligibility with consecutive recruitment of eligible participants. Recruitment is estimated to occur over 12 weeks or until the target number is reached. Participants will be included if they are (1) admitted to the ASU within 24–72 h after onset of stroke (ischemic or hemorrhagic, first and/or recurrent stroke), (2) able to complete a transfer from bed to chair with assistance of two persons or less, (3) able to follow single stage commands, (4) requiring assistance for basic activities of daily living (ADLs), and (5) were able to walk independently premorbidly (functional ambulation category score ≥4) and have a modified Rankin Score (mRS) of ≤2 from self-report. Participants will be excluded if they have (1) a retrospective premorbid mRS of ≥3, (2) a concurrent diagnosis of rapidly deteriorating disease, or (3) have an extensive psychiatric history. To allow for observational data collection, stroke survivors will also be excluded if discharge from the ASU is likely to occur within 2 days of admission. Informed consent will be obtained from participants or their substitute decision maker. Participants will be informed that the project aims to compare an alternative model of rehabilitation with the traditional model of rehabilitation, but not informed regarding the specific intervention being investigated or group allocation.

### Baseline measures

Baseline measures will include demographics; previous mRS and living arrangements; stroke details such as date, estimated time of onset, lesion location and type, Oxford Stroke Classification, and National Institute of Health Stroke Scale (NIHSS). Stroke severity will be classified according to NIHSS [21] on admission (day 1 if thrombolyzed): mild (<8), moderate (8–16), and severe (>16).

### Intervention

In the 12-week usual care block, participants will receive usual stroke management within the ASU and rehabilitation will be delivered in one-on-one interventions by therapists to stroke participants. At this site, therapists have access to a common therapy room, discipline-specific allied health assistants for individual treatment sessions and equipment to increase practice. Staffing levels will be monitored across the study period to ensure that they remain consistent across blocks.

After the usual care block, there will be a 6-week period in which the environment of the ASU will be adapted. Several communal areas will be created on the ward where participants have access to stimulating equipment. Self-directed exercise programs, iPads loaded with apps, iPods loaded with music, books, board games, puzzles, magazines, newspapers, and music will be available during and outside of therapy hours. During these 6 weeks, staff focus towards enabling activity will be reinforced through interdisciplinary education sessions. At these sessions, the EE theoretical concept, EE intervention, and ‘enablers and barriers’ of implementation of the intervention will be interactively discussed [22]. We will educate staff to encourage participants to attend communal areas and to use stimulating equipment in communal areas and at the bedside. Allied health assistants will be trained from discipline-specific to “generic” allied health assistants for the EE intervention. By doing this, all assistants will be able to mobilize patients and assist all therapists. In addition to interdisciplinary education, we will appoint nurse champions to facilitate and encourage adherence to the intervention on a day-to-day basis.

In the 12-week EE block, communal areas will be used to enhance individual and group activities. A daily group session will focus on different aspects of stroke recovery such as education, emotional support, communication, and physical activities. On three weekdays, there will be an interactive breakfast, and every weekday, an interactive lunchtime will be organized. These interactive mealtimes are aimed to increase the frequency of mobilization, encourage sitting upright for mealtimes, and stimulate social interaction. Staff present during mealtimes will facilitate independence in consuming meals and encourage nutritional intake in participants. Participants will be encouraged to voluntarily attend mealtimes without coercion for any activity. As total staffing numbers will not change with the EE, any staff time in group/meal sessions will be diverted from previous 1:1 therapy time. Allied health assistants will play the main role in managing mealtimes.

Participants of the EE block will receive a brochure that outlines the importance of frequent activity early after stroke; advice about how families can be involved and the day structure of the ASU will be explained. To encourage family involvement, stimulating equipment and individualized activity cards will be placed at the participant’s bedside tailored to the stroke survivor’s goals. Family and staff will be advised to bring personal items and hobby activities for the participant and to encourage the participant to engage in these activities outside therapy hours and on weekends.

### Fidelity of the intervention

During the EE intervention, we will monitor the occurrence of mealtimes and group sessions, availability of resources, and provision of information brochures. Our main measure for a successful implementation is to determine if participants in the EE intervention demonstrate significant higher activity levels as compared to usual care and that the EE is a safe intervention in the ASU.

### Primary outcomes

Activity levels will be determined for 'any activity', physical, social, and cognitive activity and time spent alone. Any activity is defined as the stroke survivor performing at least one physical, social, or cognitive activity or a combination of activities in these domains [23]. Total activity will be expressed as a percentage of the total number of observations performed, as will activity within physical, social, and cognitive activity domains. The first 10 days after admission will be considered as the primary exposure profile.

The behavioral mapping protocol by Janssen et al. [23] has been adapted for this study and will be used for measuring activity. Protocol adaptation included incorporating typical activities and equipment utilized in the acute setting.

Participants will be observed for 1-min at 10-min intervals from 7.30 am till 7.30 pm on two weekdays and one weekend day for a maximum of three mapping days or until discharge from the ASU. For each observation, the main activity performed during 1-min will be recorded for each category. In addition, we will report if the participant performed the observed activity independently, supervised, or with assistance. The participant’s location, body position, and people present will also be documented. Participants can be engaged in 'no activity' and can perform activities across more than one domain concurrently.

During each observation, the observer will collect data for as many categories as able. When the observer is unable to view the participant due to activity precluding direct observation (e.g., participant is in the bathroom), an attempt will be made to retrospectively estimate activity from nearby staff or the participant. Intervals where a participant is unable to be observed (e.g., off the ward for investigations) or activity unable to be estimated will be classified as 'unobserved'. Unintentional non-observations will be classified as 'missing' data. Unobserved and missing data will not contribute to the total number of observations for a participant. The reason for and proportion of 'unobserved and missing observations' will be reported by group.

Staff performing behavioral mapping will have specific training, followed by assessment compromising observation of four patients for 1 h, providing 24 observations. Competency to record study data is defined as attaining ≥90 % agreement with concurrent observations by the investigator. Behavioral mapping staff members will not receive any study details.

### Secondary outcomes

Secondary measures to be collected include functional outcomes, adverse and serious adverse events, and mood. Functional outcomes will be assessed with the mRS, modified Barthel index (MBI), 10-m walk test, and Mobility Scale for Acute Stroke patients (MSAS). Mood will be assessed with the Hospital Anxiety and Depression Scale (HADS), and nutritional status will be determined through weight and the Subjective Global Assessment (SGA) to assess for malnutrition. Serious adverse events (SAE) are defined as an adverse event that led to death and/or led to serious deterioration in health of a patient, whereas adverse events (AE) are defined as any untoward or unfavorable medical occurrence in a patient. Complications recorded include falls, pneumonia, pressure areas, cardiac problems, seizures, reduced Glasgow Coma Scale, stroke, transient ischemic attack, urinary tract infection, depression, constipation, malnutrition, delirium, and “other” including shoulder pain, deep venous thrombosis, and urinary retention [24, 25].

### Data collection time points

An investigator will conduct the initial assessment on entry to the study. Blinded assessors will perform discharge assessments immediately prior to discharge from the ASU or when a decision for palliative intent is made. Blinded assessors will also undertake follow-up phone calls at 3 months post-stroke to determine mRS, living arrangement, Health State Score [26], and if any SAEs have occurred after discharge. Three months after the EE block, another period of behavioral mapping will occur to determine whether activity levels have been sustained in the ASU. We aim to recruit 30 participants using the same eligibility criteria and complete behavioral mapping on a single, randomly chosen day from 7.30 am till 7.30 pm.

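### Discharge assessments are called blinded although block order and a visibly changed ward reveal allocation; separately, unseen intervals are estimated from a source that differs by block and count in the primary outcome

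*Protocol article*

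**What the plan says.** **Design.** Under Methods/design, 30 usual-care participants are recruited first and 30 EE participants afterwards, and "we will embed an EE in the same ASU during a 6-week period before commencement of block 2". The Intervention section states: "Several communal areas will be created on the ward where participants have access to stimulating equipment". In the EE block, "stimulating equipment and individualized activity cards will be placed at the participant’s bedside", and there are group sessions and shared mealtimes. Between the blocks, staff are taught the EE concept and how to encourage activity, and nurse champions are appointed. EE-block participants receive a brochure on the importance of being active.

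**Discharge and follow-up.** Data collection time points states: "Blinded assessors will perform discharge assessments immediately prior to discharge from the ASU". The same section also calls the 3-month telephone assessors blinded. It describes no masking procedure for either.

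**Primary outcome.** Activity is recorded by behavioural-mapping staff. They are never called blinded; the text says only: "Behavioral mapping staff members will not receive any study details". If what the participant is doing hides them from view, "an attempt will be made to retrospectively estimate activity from nearby staff or the participant". Intervals that cannot be estimated, or when the participant is off the ward, are classed as unobserved and leave the denominator. Reasons and proportions are promised by group for unobserved and missing intervals. No such reporting is stated for intervals that were estimated.

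**The concern.** There are two separate issues, affecting different outcomes.

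1. **Discharge outcomes (secondary).** Every block 2 participant is an EE participant. An assessor who sees the ward, or who knows the block dates, therefore knows the allocation. Several of the measures listed under Secondary outcomes need rater judgement (modified Rankin Scale, modified Barthel Index, Mobility Scale for Acute Stroke), so the word blinded would carry weight with readers of the report.

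2. **Activity levels (primary).** The people who supply the estimates for unseen intervals are in a different position in the two blocks. In block 2, staff have been trained to promote activity and participants have been told in writing that it matters; in block 1, neither applies. Any resulting difference in reporting goes straight into the numerator of the primary outcome. The Sample size section plans a one-sided test towards EE, and Fidelity of the intervention makes significantly higher activity part of the main measure of success. A false shift in that direction would affect both conclusions. Because estimated intervals are not identified, a reader of the report could not judge how much rests on them.

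**Working it through.** **Step 1: can discharge assessors be blind as described?** Set side by side, the sections give one ward, one condition at a time, a physical change to the ward and bedside, and assessment just before the patient leaves that unit. Masking would need assessors who do not know of the before-after design or the block dates and who do not see the ward. Neither condition is stated.

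**Step 2: do the telephone calls escape the problem?** Inputs: blocks of about 12 weeks (Abstract; Participants and setting), a 6-week gap (Methods/design), and calls 3 months after stroke, taken as about 13 weeks.
- Block 1 recruits in weeks 0 to 12, so calls fall at about weeks 13 to 25.
- Block 2 recruits in weeks 18 to 30 (12 + 6 = 18), so calls fall at about weeks 31 to 43.

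The two call periods do not overlap. The caller does not see the ward, but the call date identifies the block for anyone who knows the schedule.

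**Step 3: reproduce the plan's own figure.** Inputs from Sample size: increases of 13 (SD 14) and 2 (SD 16.5), one-sided alpha 0.05, power 0.8, dropout 12%.
- Difference = 13 − 2 = 11 points.
- Pooled SD = √((14² + 16.5²)/2) = √234.125 = 15.30.
- Effect size = 11/15.30 = 0.719, rounded in the plan to 0.7.
- One-sided n at 0.7 = 26 per group (exact t-test power 0.801).
- 26/(1 − 0.12) = 29.5, so 30 per group.

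The stated figures reproduce; no number in the document is wrong on this point.

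**Step 4: what would a false shift do?** Suppose there is no true effect, but the EE block is overstated by b points. The actual one-sided error is P(T > t₀.₉₅), where T has a noncentral t distribution with 2n − 2 degrees of freedom and noncentrality (b/15.30) × √(n/2). At n = 26, √13 = 3.606.

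| b (points) | Noncentrality, n = 26 | Error, n = 26 | Error, n = 30 |
|---|---|---|---|
| 1 | 0.236 | 0.079 | 0.082 |
| 2 | 0.471 | 0.119 | 0.126 |
| 3 | 0.707 | 0.172 | 0.186 |

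**Step 5: what would produce such a shift?** Let u be the share of counted intervals that were estimated, and e the net excess probability in the EE block that an estimated interval is coded active. Then b = 100 × u × e. Assumed values only:
- u = 0.05, e = 0.2 gives 1 point.
- u = 0.10, e = 0.2 gives 2 points.
- u = 0.10, e = 0.3 gives 3 points.

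A full record is 12 × 6 × 3 = 216 intervals, so 1 point is about 2 intervals per participant (0.01 × 216 = 2.2) and 3 points about 6 (0.03 × 216 = 6.5). The documents give neither u nor e.

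**The case against.** **On blinding.** The discharge sentence fixes a time, not a place, and an article may leave masking procedures to the full protocol. An assessor who knows nothing of the design could remain naive. That stands, and it is why the conclusion is that the claim is unsupported as described. A reader might go further and call it false; the text does not show that.

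A reader might also infer that the primary outcome is presented as blinded. It is not: the discharge sentence concerns secondary outcomes, and mapping staff are said only to receive no study details.

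**On estimated intervals.** The route is narrow: an attempt, made only when activity prevents direct view, with the bathroom as the example. The source may be the participant rather than staff, and Participants and setting says participants are not told the specific intervention or their group. Mapping staff must reach at least 90% agreement with the investigator. These safeguards reduce the risk, but the agreement check covers concurrent observation, not retrospective estimates. The direction is plausible, not proven: if such intervals were mostly coded active in both blocks, there would be little room for a difference.

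**On size.** A reader might combine pessimistic guesses (15% of intervals estimated, each overstated by 30 points in the EE block alone) into 0.15 × 30 = 4.5 points, or 4.5/11 = 41% of the planned effect. That is the extreme corner of assumed inputs, and the documents support neither.

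**On the remedy.** Restricting the primary analysis to directly seen intervals would drop intervals because of what the participant was doing, possibly at different rates by block. That objection stands, so the planned primary analysis should stay.

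**Conclusion.** Both points hold in limited form.

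1. The blinding of discharge assessments is not supported by the design as described. The 3-month calls are better placed, since the caller does not see the ward, but their blinding also depends on ignorance of the design and block dates.

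2. Estimated intervals bring into the primary outcome a source of information that differs by block and could plausibly favour EE. The size cannot be derived from the documents. The range of about 0.08 to 0.17 for a 1 to 3 point shift at 26 per group is an illustration. It assumes no true effect, an SD of 15.3 taken from the rehabilitation study, an unadjusted comparison, and that the one-sided test in Sample size carries over to the covariate-adjusted analysis. It shows only that modest shifts matter at this sample size.

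The sample size is unaffected. What changes is how far the discharge results can be called blinded, and whether a reader can see how much of the activity result rests on second-hand report.

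**What to change.** - **Discharge assessments.** State how assessors are masked (for example, unaware of the before-after design and block dates, and assessing away from the ward), or do not report these outcomes as blinded.
- **Telephone calls.** State that callers are kept unaware of the design and block dates; otherwise drop the word for them too.
- **Mapping.** Acknowledge that observers can see the ward condition.
- **Estimated intervals.** Add a source code to each interval: seen, staff report or participant report. Report estimated intervals by block alongside the unobserved and missing ones.
- **Analysis.** Keep the planned primary analysis and add a prespecified sensitivity analysis excluding estimated intervals.

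For the mapping and analysis changes, the cost is some wording, one tick-box on the mapping sheet and one extra analysis. Masking discharge assessors, if chosen over dropping the word, also needs suitable staff and a place off the ward. The sensitivity analysis itself drops intervals for activity-related reasons, so it should be read together with the primary analysis and not in its place.
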